The Brazilian conditional cash transfer (CCT) program, Bolsa Familia Program (BFP), is the world`s largest CCT and targets poor households earning between US$18–36 per person per month. Eligibility is assessed at the federal level to minimize errors and fraud. The monthly cash benefits range from US$17 to a maximum of US$41 (depending on household size and composition) and payments are credited directly to a beneficiary debit card [17, 18]. Conditions for receipt of the benefits include: attendance at prenatal and postnatal monitoring sessions; children aged 0–7 must be up-to-date with nutrition monitoring and immunizations, and children must attend school. Previous studies have assessed the effectiveness of the BFP on child morbidity and mortality and a host of other conditions, from suicide and tuberculosis to leprosy [19–23]. Brazil has also implemented over the last two decades one of the most consolidated and evaluated Primary Health Care (PHC) programs, the Family Health Strategy (FHS), in a comprehensive approach to providing PHC as part of Brazil’s National Health Services, the Unified Health System (SUS) [24]. These facilities are open to all Brazilian citizens and are located within community settings close to where people live. Several studies have evaluated FHS effectiveness, demonstrating that expansion of the FHS has contributed to better health outcomes, including reducing infant and adult mortality, decreasing unnecessary hospitalizations, enhancing health system functions such as recording of vital statistics, and decreased inequities in both healthcare access and health outcomes [25–32].

Brazil is also an extremely data-rich country, where demographic, socioeconomic and interventions coverage data are available in terms of both quantity and adequate quality. Several impact evaluations of CCT have been performed using publicly available secondary aggregate-level longitudinal data and, more recently, individual-level data using the 100 Million Brazilian Cohort [33]. For these reasons Brazil provides a unique opportunity to study the effects of changes in socioeconomic determinants, CCT and PHC on a such complex and chronic infectious disease as HIV/AIDS in LMIC. Therefore, the detailed objectives of the proposed study are described as follows:

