### Data and measures

This study builds upon the integration of a wide range of datasets. The aggregate-level longitudinal data on municipalities conditions, infrastructures, healthcare coverage and morbidity and mortality levels will be integrated with large individual-level dataset constituted by the linkage between AIDS-specific clinical and treatment longitudinal data with the 100 Million Brazilian Cohort, built by the Centre for Data and Knowledge Integration for Health (CIDACS), Salvador, Brazil [40, 41]. Fig 2 illustrates the different datasets linked and the different population groups that will be compared. The cohort has information of over 100 million individuals that were registered during 2000 and 2018 in *Cadastro Unico* (*CadUnico*), a national administrative system containing information on all individuals, and their families, applying for any social programs in Brazil [42]. To be eligible for registration in CadUnico, families must earn a per capita income of up to half the minimum wage or a total familial income of up to 3 times the minimum wage (e.g., minimum wage ranged from 380 BRL in 2007 to 724 BRL in 2014). By the end of 2018, the CadUnico contained approximately 114 million individual registrations, representing just over 50% of the Brazilian population. At registration, enrollees are assigned a unique numerical identifier and surveyed regarding socioeconomic indicators. The CadUnico collects information about housing conditions, income and demographic characteristics of all the members of a family registered. The CadUnico cohort includes 246 variables with information from the family and individuals registered in this data collection and storage system [43]. The data include socioeconomic aspects such as income, occupation, and employment status; demographic characteristics such as age, schooling, ethnicity, marital status, family composition, and number of families in the same household; living conditions such as number of rooms in the house, housing material, household water supply, sewage disposal system, electricity in the home, and waste collection; as well as information regarding health status as presence of a mental health disorder, disabilities and access to healthcare services. The CadUnico also holds information about who has received the BFP benefit, when it was received, and the total amount received per month.

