**Step 1**. To analyze the differential impact and dose-response of BFP according to the duration of the intervention, amount of money received and compliance with conditionalities. The retrospective impact evaluation will use arguably one of the most robust study designs for causal inference in quasi-experimental studies: the regression discontinuity design (RDD), which allows a quasi-randomization of the subjects under study around the eligibility threshold [52, 53]. The eligibility of the BFP is determined by two thresholds: one for poor families (below 154 BRL *per capita*) with vulnerable members (children or pregnant women), the second for extremely poor families (below 77 BRL *per capita*), even without any vulnerable member. BFP is one of the most accurately targeted CCTs, and if inclusion/exclusion errors are identified, a fuzzy-instead of sharp-RDD will be used. The presence of two different cut-offs will allow to evaluate the different impact of the BFP on the two different thresholds: between eligible and non-eligible poor and eligible and non-eligible extremely poor families. In order to explore the impact in subjects outside of the RDD selected bandwidth, analyses using Random Administrative Delays (RAD) and Propensity Score Matching (PSM) [54–56] will also performed. These methods have been already used for similar studies with the CadUnico to evaluate the effects of BFP on Tuberculosis (TB). The PSM has also been used in with the same linked dataset to complementarily evaluate the impact of BFP on TB cure and mortality rate [21]. Where possible, combination of these designs—such as the PSM-RDD—will be used [57]. The complementary use of the three methods will consequently allow to assess the effects of BFP along the complete range of socioeconomic conditions represented over the 100 million individuals of the dataset. All analyses above will be stratified according to the years of exposure to BFP and amount of received money over the 12 years of follow-up, to evaluate a dose-response relation with the duration and intensity of support received. Analyses will also explore lagged effects by associating exposures of previous years with outcomes of a range of following years.**Step 2**. To measure the BFP impact on a broad and detailed range of different subpopulations defined by individual demographic and socioeconomic characteristics and by local geographic regions, and municipality development. The evaluation designs and methods described above will be used for stratified analyses with each subpopulation of interest: age groups, gender, illiteracy and educational level. Further stratifications will be based on the characteristics of the municipality: human development index, GDP per capita and Gini index of income inequality.**Step 3**. To analyze the dose-response of FHS according to the extent and duration of the municipal coverage. Using the same structured dataset from the previous analyses of Aim 2, and considering that coverage of FHS is only available at the municipal level, the FHS impact will be evaluated using a Propensity Score (PS) weighted multilevel negative binomial regression design with individual level-variables from Aim 1, including BFP as adjusting variable [56]. To avoid ecologic fallacy, the dataset will be resized and limited to municipalities with 90–100% (consolidated FHS coverage = exposed) and 0–10% FHS coverage (low/insignificant FHS coverage = control) in the study period. The intervals 0–10% and 90–100%, instead of 0% and 100%, will be used to consider uncertainty in the coverage measure, but sensitivity analyses will be performed with 0% and 100%.**Step 4**. To measure the FHS impact on a broad range of different subpopulations defined by individual demographic and socioeconomic characteristics and by local geographic regions. As in the Step 2 of the Aim 2, the evaluation designs and methods will be used for each subpopulations of interest: age groups, gender, illiteracy and educational level. Moreover, further stratifications also will be based on the characteristics of the municipality.**Step 5**. To evaluate the synergistic individual-level exposure to BFP with municipal-level coverage of FHS on incidence and mortality from HIV/AIDS. Using the same multilevel and multivariable regression models above, the interaction effects of BFP with FHS will be evaluated with product terms and stratification analyses.

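### The money-based dose-response for the Bolsa Familia Program (BFP) is confounded with household type, because the amount paid depends on household size and composition

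*Protocol article*

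**What the plan says.** Four statements in the protocol article bear on the dose.

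- **Analysis** (Analytic strategy, Aim 2, Step 1): the regression discontinuity (RDD), random administrative delay (RAD) and propensity score matching (PSM) analyses are to be "stratified according to the years of exposure to BFP and amount of received money over the 12 years of follow-up". The purpose is to "evaluate a dose-response relation with the duration and intensity of support received".
- **What sets the amount** (Introduction): "The monthly cash benefits range from US$17 to a maximum of US$41 (depending on household size and composition"). No other determinant is named.
- **What is recorded** (Data and measures): who received BFP, "when it was received, and the total amount received per month".
- **Who qualifies** (Analytic strategy, Step 1): two income cut-offs per head, "one for poor families (below 154 BRL *per capita*) with vulnerable members (children or pregnant women") and "the second for extremely poor families (below 77 BRL *per capita*), even without any vulnerable member".

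No section scales the amount by household size or examines the dose-response within household types. The Step 2 subgroups are age, gender, illiteracy, education and municipality characteristics. The Aim 1 covariate blocks include household density but not family size or number of children. Family composition is listed among the CadUnico variables.

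**The concern.** A dose-response analysis needs families that are alike except for the dose. Here the programme's rule, as the article describes it, gives different amounts to different kinds of family. If duration of receipt is held fixed, the only stated reason for one family to receive more than another is that it is larger or differently composed. Ordering recipients by money then largely orders them by household type.

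The money gradient is one of the stated purposes of Step 1, and readers would take it as evidence on whether a larger benefit does more. A gradient produced by family type would answer that question wrongly in either direction: it could suggest a benefit of larger payments where there is none, or hide one that exists.

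The eligibility rule adds a further link. A family with no child or pregnant woman qualifies only below the lower cut-off, so among recipients household type is also tied to depth of poverty.

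**Working it through.** The article gives no power or precision figure for this analysis, so there is none to reproduce. The check has three parts.

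**1. What a between-stratum gradient estimates.** Take two household types, S (small, low amount) and L (large, high amount). Let λ be the outcome rate without BFP and θ the true rate ratio for BFP in that type.

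- *Undivided control group with rate λ̄.* Non-recipients have no received amount, so they cannot be sorted by it. The estimated ratio in type t is θ_t × λ_t / λ̄. The gradient between strata is (θ_L / θ_S) × (λ_L / λ_S). The second factor is baseline risk by family type and has nothing to do with cash.
- *Controls matched on composition within each stratum.* The second factor cancels and θ_L / θ_S remains. To the extent that amount is set by type, this ratio cannot be split into an effect of more money and a difference in how BFP works in different families.

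The three designs address receipt, not amount. RDD makes families comparable on either side of an income cut-off. If the recipient side is then restricted to one money stratum, it is restricted to certain household types, while the non-recipient side is not. RAD exploits the timing of payment. PSM can balance composition only if composition is among the matching variables.

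**2. Whether the order of per-person support can reverse.** Inputs are the stated US$17 and US$41. Household sizes are not given and are assumed. Per-person amount = monthly amount / household size. The top-amount household has less per head when

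41 / n_L < 17 / n_S, that is, n_L / n_S > 41 / 17 = 2.41.

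| Size at US$17 | Size at US$41 | Per head at US$17 | Per head at US$41 | Reversed? |
|---|---|---|---|---|
| 1 | 3 | 17.00 | 13.67 | yes |
| 2 | 4 | 8.50 | 10.25 | no |
| 2 | 5 | 8.50 | 8.20 | yes |
| 3 | 6 | 5.67 | 6.83 | no |
| 3 | 7 | 5.67 | 5.86 | no |
| 3 | 8 | 5.67 | 5.12 | yes |

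As a range check, assume the benefit rises linearly from US$17 at the smallest household (1, 2 or 3 persons) to US$41 at the largest (4 to 8 persons). Of the 15 combinations, the per-person amount falls as the total rises in 10 and rises in 5. Five of the 10 start from a one-person household. The article does not say what such a household receives. Leaving those out, the split is 5 and 5.

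**3. Why duration must be held fixed.** At constant payment, 12 years give 17 × 144 = US$2,448 at the minimum and 41 × 144 = US$5,904 at the maximum. About 12 × 17 / 41 = 5.0 years at the maximum equals 12 years at the minimum. An amount cumulated over follow-up therefore mixes duration with household type. Fixing duration removes the first and leaves the second.

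**The case against.** The strongest reply is that the plan does not compare crude rates across money strata. It stratifies quasi-experimental contrasts, and the article argues in its limitations paragraph that RDD and PSM use controls comparable to the exposed. If controls are comparable within each stratum, baseline risk cancels, and with no cash effect every stratum is null. This stands in part. A reader might infer that a gradient must appear even when cash does nothing. The article does not support that, because matching on composition within strata would prevent it. But such matching is not stated, it does not follow from the designs themselves, and it would still leave effect differences by family type inside the gradient.

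A second reply is that an article condenses, so the scaling of the dose and the matching covariates may be set out in a fuller document. For the covariate list that is fair. The choice of received money as the measure of intensity is stated, however, and the article's own account of how the benefit is set makes it a problem.

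Third, per-head money is not the one true dose. Household total, per-member amount or share of income could each be defended, and per-capita eligibility beside household payment is no contradiction. This stands: the point does not depend on preferring a per-person scale.

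Fourth, Step 2 stratifies by age and gender, which removes part of any difference in who lives in high-amount households. It does not separate household types within an age and gender group.

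A reader might also infer that the Aim 3 forecasts inherit the error. The scenarios described there vary BFP and FHS coverage, not benefit amount, and no dose-specific effect is said to enter the model.

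**Conclusion.** The concern holds for the money dose-response. As planned, amount and household type cannot be told apart at a fixed duration, so a gradient in total money is not interpretable as an effect of intensity. This rests on the article's statement that the benefit depends on household size and composition. If other sources of variation exist, such as changes in benefit levels over time, the confounding is partial, and that variation is what the analysis should use.

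The direction and size of any bias cannot be computed, because the article gives neither household sizes by amount nor outcome rates by family type. Reversal of the per-person order needs a size ratio above 2.41. It is possible, but a reader should not take it as shown. The comparisons of recipients with non-recipients and the analysis by years of exposure are outside this point.

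**What to change.** In Aim 2, Step 1:

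1. Define classes of household size and composition from the CadUnico family data. Compare amount levels only within a class, at a given duration of receipt.
2. Draw or match controls from the same class in each of the RDD, RAD and PSM analyses, and state composition as a matching variable.
3. Report the amount per household member beside the total amount.
4. State that a gradient in total money across household types will not be interpreted as dose-response. Where the benefit is fully determined within a class in a given period, rely only on changes in its level over time, or report that the dose-response cannot be estimated there.

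The cost is small in data terms: one derived variable and one stratifier from information already held. The statistical cost is real. Amounts vary less within a class, so intervals will be wider, and some classes may offer no usable contrast.

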**Fig 3 pone.0265253.g003:**
[figure not shown]
Integrated microsimulation, compartmental and agent-based model.

For each outcome and each scenario, 10,000 Monte Carlo simulations will be performed allowing all parameters to vary by their underlying distribution—measured in the retrospective analysis—and consequently obtaining the Predictive Intervals of each estimate. The linear regression of predicted versus observed values and the proportion of variance (R^2^) explained will be assessed, and will be verified that all observed values will be included in the 95% CIs of the simulation estimates, among other validation criteria [69, 70].

Once the MS-CM-ABM models are validated, we will use them to:
Forecast the prolonged effects of the ongoing increases in poverty rates due to the economic crisis and the impact of reductions in BFP and FHS coverages due to the currently implemented fiscal austerity measures, versus different dynamics of improved socioeconomic scenarios and stabilization or increases in BFP and FHS coverage up to 2030.Evaluate in which specific subpopulation groups increased BFP and FHS coverage could be more beneficial. Using the granularity of MS-ABM and subpopulation specific effect estimates from the retrospective evaluation several scenarios of expansion of BFP and FHS in target populations will be tested, and the benefits compared.Evaluate with comprehensive calibration which combination of socioeconomic determinants changes and BFP and FHS subpopulations coverage will allow to reach AIDS-related Sustainable Development Goal 3.3 in Brazil. Using the comprehensive set of scenarios evaluated above, the combinations of socioeconomic changes and interventions expansions will be more finely tuned to maximize the chances to reach the end of HIV/AIDS epidemic in Brazil.

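### Aim 2, Step 3 promises an FHS dose-response by extent of coverage but keeps only municipalities at 0–10% and 90–100%, so only a high-versus-negligible contrast can be estimated; duration depends on an undefined band rule

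*Protocol article*

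**What the plan says.** All of this is in the protocol article, Materials and methods, Analytic strategy.

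- **Objective of Aim 2, Step 3:** "To analyze the dose-response of FHS according to the extent and duration of the municipal coverage". Two dose dimensions are named, extent and duration.
- **Data kept:** the analysis is "limited to municipalities with 90–100% (consolidated FHS coverage = exposed") and "0–10% FHS coverage (low/insignificant FHS coverage = control) in the study period". The stated reason is to avoid ecologic fallacy, because FHS coverage is known only at municipal level.
- **Spread inside the bands:** the 10-point widths "will be used to consider uncertainty in the coverage measure, but sensitivity analyses will be performed with 0% and 100"%. Variation within a band is thus treated as measurement uncertainty, and the one sensitivity analysis narrows the bands further.
- **Model:** a "Propensity Score (PS) weighted multilevel negative binomial regression design with individual level-variables from Aim 1, including BFP as adjusting variable". Step 3 names no term for coverage level or duration. Step 1, by contrast, states strata by years of exposure and amount received for BFP.
- **Later use:** the Aim 3 text after Fig 3 lists forecasts of "the impact of reductions in BFP and FHS coverages", set against stable or rising coverage up to 2030.

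**The concern.** The objective and the data rule sit in the same step and do not fit together. A dose-response by extent needs observations at several levels of coverage. The rule leaves two levels, labelled exposed and control. This is not detail that a condensed article leaves to a fuller plan, because the article itself fixes the restriction.

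Duration has a different problem. The restriction acts on coverage level and does not by itself remove variation in years at high coverage. Whether such variation remains depends on the words about the study period that close the data rule. They could mean membership judged year by year, or membership throughout 2000–2018.

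Two things are at stake. Step 3 could report a two-group contrast under the name of a dose-response. And Aim 3 needs the effect of partial changes in coverage, which generally fall in or cross the excluded range.

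**Working it through.** The protocol article gives no sample size, event count or effect size for this step, so there is no figure of its own to reproduce. The check asks what the retained data can identify.

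**1. Extent**

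Inputs from the article: bands 0–10% and 90–100%. The excluded range is 90 − 10 = 80 of 100 percentage points. That is a width on the coverage scale, not a share of municipalities or person-time, which the article does not give.

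Assumptions for illustration: band midpoints 5% and 95%; rate ratio 0.80 between them, so b = ln 0.80 = −0.223; three curves f(x) for the log rate ratio at coverage x relative to 5%.

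- Linear: f(x) = b(x − 0.05)/0.90
- Threshold at 70%: f(x) = b if x ≥ 0.70, otherwise 0
- Saturating: f(x) = b[1 − exp(−8(x − 0.05))]/[1 − exp(−8 × 0.90)]

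| Curve | RR, 95% vs 5% | RR, 50% vs 5% |
|---|---|---|
| Linear | 0.800 | exp(−0.223 × 0.5) = 0.894 |
| Threshold | 0.800 | 1.000 |
| Saturating | 0.800 | 0.805 |

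The planned contrast is the same for all three, so the retained data cannot tell them apart. Using the spread within the bands as dose would not help, since it carries no information between 10% and 90%.

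**2. Consequence for a coverage scenario**

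Take an illustrative cut from 65% to 50%; these levels are not in the article. A straight line between the midpoints assigns (65 − 50)/(95 − 5) = 15/90 = 17% of the full log-effect. A threshold outside 50–65% gives 0%, and a threshold inside gives 100%. With the assumed 0.80, the rate would rise by a factor of 0.80^(−0.167) = 1.04, 1.00 or 1/0.80 = 1.25 respectively.

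**3. Duration**

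Setup: 19 calendar years (2000–2018), 200 hypothetical municipalities per group, and a design matrix with intercept, exposure, years at 90% or more, and 18 year indicators (21 columns).

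| Reading of the band rule | SD of final-year duration among exposed | Correlation of duration with calendar year among exposed | Rank |
|---|---|---|---|
| In band throughout 2000–2018 | 0 | 1.0 | 21 of 21 |
| Entry to 90–100% in varying years (assumed 2000–2014) | 4.28 years | 0.58 | 21 of 21 |

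Under the first reading every exposed municipality has duration = year − 1999. The matrix keeps full rank only because the gap between exposed and control can change over calendar time. A duration effect is then indistinguishable from an exposure effect that drifts with time.

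Under the second reading duration varies between municipalities in the same year and is estimable. One limit remains: years spent between 10% and 90% are outside the data. A municipality that reaches 90% after ten years at 80% would count as newly exposed.

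**The case against.** **The restriction is deliberate and has a reason.** Near 0% or 100%, municipal coverage approximates individual coverage, and a sensitivity analysis at exactly 0% and 100% is planned. This stands as a case for keeping the extreme contrast. It does not make that contrast a dose-response.

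**Aim 3 models individuals.** Partial coverage could be represented as the share of people covered, using a covered-versus-uncovered effect. The article also says that model inputs will be integrated with parameters from nationally representative studies. The first point is fair but is itself an assumed shape: rates linear in coverage, which in the example above gives 1 − 0.20 × 0.5 = 0.90 at 50%. It holds only without spillover or threshold effects. The article does not say that the outside parameters would supply FHS effects at intermediate coverage.

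**Duration coding is detail for a fuller plan.** This stands in part. A missing formula is not a finding here. The ambiguity of the band rule matters because it decides whether the stated duration objective can be met.

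**Stronger readings that the document does not support.**

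- *Neither dose dimension can be estimated, and every municipality that rolled out FHS is dropped.* This would follow only under the whole-period reading, which the text does not settle. The abstract also promises lagged and long-term effects of changes in FHS exposure.
- *The contrast rests entirely on propensity weighting, where overlap is poorest.* The model also adjusts for individual-level variables and BFP. No municipal covariate or coverage distribution is given, so overlap is something to check and not a shown defect.

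**Conclusion.** The point holds in this form. As written, Step 3 cannot deliver a dose-response by extent of coverage; it can deliver one high-versus-negligible contrast. This follows from the stated data rule and needs no numerical assumption. The duration objective is conditional: it can be met if municipalities enter the upper band in different years, and it is confounded with calendar time if membership must hold for the whole of 2000–2018.

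The size of the consequence for Aim 3 is illustrative. With an assumed rate ratio of 0.80 across the bands, the rate ratio at 50% coverage ranges from 0.805 to 1.000 over the three curves examined. The rate ratio, curve shapes, entry years and the 65%-to-50% cut are assumptions. Simulation intervals that draw only on parameter distributions from the restricted analysis would leave out this uncertainty about shape.

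**What to change.** 1. Keep the 0–10% versus 90–100% analysis and its sensitivity analysis at 0% and 100%, and label it high versus negligible coverage.
2. State whether band membership is judged yearly or over the whole period, and define duration as years at consolidated coverage.
3. Add a secondary model using all municipalities, with annual FHS coverage as a time-updated exposure (bands or a spline over 0–100%) and years at consolidated coverage as the duration term.
4. For Aim 3 scenarios at partial coverage, use the full-range model or a stated range of curve shapes.
5. If no full-range model is added, drop the claim of a dose-response by extent.

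The cost is a change of wording and one further model on municipal coverage data that the study already relies on. The downside is that individual exposure is misclassified at intermediate coverage, so full-range estimates may be biased; this is why that model should be reported as secondary. Its difference from the extreme contrast should not be read as pure attenuation, because it would mix attenuation, non-linearity and different confounding.
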